### Statistical Analysis

A statistician who is not affiliated with this study will perform the statistical analyses for Linear random effects modeling—which accounts for repeated measures over time—that will be used to study the intervention’s effect [24]. We will also use multilevel modeling to describe within-person differences in anxiety and depression. We will then compare this observed trajectory with the control group’s trajectories.

The level of change in anxiety from weeks 0-26 (baseline to final assessment) over the 6 months’ time period is the primary trajectory of concern for mental health in this study. We will test the hypothesis that the trajectories are changing over time and the intervention’s effects are expected to be observed as changes in self-reported mood, which will be measured with the mood scores, cutoff scores, sensitivity, etc, obtained at various time points. Interactions by demographic subgroups (primarily age, gender, race, and socioeconomic status) will be assessed for identifying potential effect modifications.

Analysis will be based on the intention-to-treat principle, as this method allows to draw an unbiased conclusion regarding the effectiveness of an intervention. It also preserves the benefits of randomization, which cannot be assumed when using other methods of analysis [25]. Further, this method is also more effective in accommodating missing data, as missingness is assumed at random.

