### Sample Size

The target sample size for the population survey and learning systems sample is 2000. This sample size will also allow for the estimation of the impact of the dashboard and app recommendations on score trajectories of the PHQ-9 and 7-item Generalized Anxiety Disorder Scale (GAD-7). Based on an estimated effect size of Cohen *d*=0.17 for changes in the PHQ-9 score and Cohen *d*=0.13 for changes in the GAD-7 score (based on the expected effects of the dashboard) [15], an expected dropout rate of no more than 35% [16], and population mean and SD estimates of PHQ-9 and GAD-7 scores [17,18], we estimate having a power of 0.90 and a type I error rate of 0.05 for detecting improvements in PHQ-9 and GAD-7 scores for subsamples with at least 1000 participants. Therefore, in this study, we will have a sample size of a total 2000 participants, with 1000 randomized to each group.

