### Outcome Measures

#### Primary Outcomes

The primary outcomes are the changes in trajectories of mental health, primarily anxiety at baseline (week 0) until final assessments (week 26) between 6 months after invitation to the WTC intervention or usual care. The trajectories are also measured biweekly with short follow-ups at different time points from week 2 until week 26. We will use multilevel modeling to describe within-person differences in anxiety and depression at different time points. We will compare the observed trajectory with those of the control group. Interactions by demographic subgroups (primarily age, gender, race, and socioeconomic status) will be assessed for identification of potential effect modifications. 

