## Results

The study is ongoing and the first wave data collection is complete; we are analyzing data from the baseline and weeks 2-26. The study is ongoing at week 26, we have analyzed the preliminary baseline data and weeks 2 and 4 short and long follow-ups to understand the ongoing trajectory of depression. Until now, 453 individuals in the age group of 18-72 years have responded to the study invitation emails.

The trial is currently in the ethics approval process. Thus far, ethics approval has been granted by the REB of CAMH, and participant recruitment is ongoing. The study will be conducted in accordance with the REB-approved study documents and the determinations (including any limitations) of the REB, and in compliance with the REB’s requirements.

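### The primary endpoint is stated as anxiety and then as an open list of mood measures, so the 0.05 error rate is not protected

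*Protocol article*

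**What the plan says.** All places are in the protocol article.

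- **Statistical Analysis.** Change in anxiety from baseline to the week-26 assessment is singled out as primary. The following sentence then locates the intervention's effect in "changes in self-reported mood, which will be measured with the mood scores, cutoff scores, sensitivity, etc, obtained at various time points". The same section plans a linear random-effects model for repeated measures and a multilevel description of both anxiety and depression, to be compared with the control group.
- **Primary Outcomes.** "The primary outcomes are the changes in trajectories of mental health, primarily anxiety". Depression is again modelled next to anxiety.
- **Sample Size.** 1000 participants per group, with "a power of 0.90 and a type I error rate of 0.05 for detecting improvements in PHQ-9 and GAD-7 scores". The inputs are an "estimated effect size of Cohen *d*=0.17 for changes in the PHQ-9 score", 0.13 for GAD-7, and dropout of at most 35%. No split or order of the 0.05 between the two scales is given.
- **Results and Discussion (Anticipated Findings).** The team has analysed baseline and "weeks 2 and 4 short and long follow-ups to understand the ongoing trajectory of depression", and reports a decline in mental health on the SF-12 from baseline to follow-up.

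**The concern.** Two adjacent sentences give different answers to the question of what shows that the portal works. Anxiety is not the same construct as mood, a score is not a cutoff, and a list ending in an open "etc" has no last member. The word sensitivity is undefined: it might mean a diagnostic property, responsiveness to change or a sensitivity analysis, and none of these is a treatment outcome as written. The other sections do not settle the matter, because one uses the plural for primary outcomes and another gives one error rate to two scales.

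Research question 1 asks whether the portal alters mental health trajectories, chiefly anxiety, relative to usual care. If a benefit on anxiety or on depression could equally be reported as the primary result, the answer would not carry a 5% error rate. The ambiguity also has a direction. On the plan's own effect sizes, depression is the easier scale to win on and anxiety the harder.

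**Working it through.** **Inputs.** From Sample Size: error rate 0.05, d = 0.17 (PHQ-9), d = 0.13 (GAD-7), 1000 per arm, 35% dropout, so 1000 × 0.65 = 650 per arm. Assumptions: two-sided tests (sidedness is not stated), standard deviation 1 on the d scale, and a between-scale correlation from 0 to 0.8.

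**1. The plan's own figures.** The 0.05 is a design input and cannot be derived. The stated power of 0.90 can be checked with power = Φ(d·√(n/2) − 1.96).

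- GAD-7, n = 650: 0.13 × √325 = 2.344; 2.344 − 1.96 = 0.384; power 0.649.
- GAD-7, n = 1000: 0.13 × √500 = 2.907; 2.907 − 1.96 = 0.947; power 0.828.
- PHQ-9, n = 650: 0.17 × √325 = 3.065; 3.065 − 1.96 = 1.105; power 0.865.

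The 0.90 is therefore not reproduced by a simple two-sided comparison of arms after dropout. One-sided, the figures at 650 per arm are 0.758 (GAD-7) and 0.922 (PHQ-9). Two variants come near 0.90 for GAD-7: a one-sided test with no dropout (0.897) and a within-person change in 650 people (0.912). The first ignores the stated dropout, and the second does not compare arms.

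**2. Error rate if one test is primary.** A single test of anxiety change at 0.05 has error rate 0.05.

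**3. Error rate if success on any of k unadjusted measures may count.** For independent measures this is 1 − 0.95^k. For equally correlated normal test statistics it was simulated (1,000,000 draws, share with any |z| > 1.96).

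| Measures | corr. 0 | 0.5 | 0.7 | 0.8 |
|---|---|---|---|---|
| 2 | 0.098 | 0.091 | 0.083 | 0.078 |
| 3 | 0.143 | 0.125 | 0.110 | 0.098 |
| 4 | 0.185 | 0.156 | 0.131 | 0.114 |

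Only the two-measure row has a direct basis in the text (anxiety and depression). The other rows show the direction if the open list were used.

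**4. What each remedy does to power (650 per arm, simple two-sided comparison).**

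- One primary, GAD-7 at 0.05: 0.649.
- Two primaries with Bonferroni 0.025 each: 0.541 for GAD-7 and 0.795 for the depression score.
- One primary, GAD-7, with baseline adjustment, replacing the standard deviation by √(1 − r²): 0.772 at r = 0.5 and 0.907 at r = 0.7. This assumes that d is scaled to the standard deviation of the score itself. The value of r is not in the document.

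**The case against.** The strongest reply is that anxiety comes first in the research questions, in Primary Outcomes and in Statistical Analysis, and the last of these gives it a window. On that reading one test is primary, 0.05 holds, and the following sentence is merely loose. Multiplicity rules and the exact contrast may also sit in a full protocol or analysis plan that is not shown. Much of this stands. A reader might infer that the 0.05 is already exceeded, but no sentence says that success on any one of several measures will count, so the excess is conditional. The absence of a multiplicity rule is not itself the point. What remains is that the printed text gives two incompatible statements of where the effect will be judged, and an unseen plan would have to contradict one of them.

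Two further stronger readings are tempting:

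- **Separate tests at every visit.** The mention of various time points could suggest this. The planned random-effects model uses all visits together, and the phrase can simply describe the repeated measurements that feed it.
- **Compromise by looks at follow-up data.** Results and Discussion describe depression trajectories and SF-12 change in the sample. They report no comparison by arm, no GAD-7 result and no change of endpoint. The Blinding section says the team is blinded, and an unaffiliated statistician is to do the analysis. The 453 participants are dated August 2023, before the stated trial window of October 2023 to April 2024, so it is unclear whether these data belong to the randomised comparison. A look pooled over arms does not by itself inflate the error of a between-arm test.

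**Conclusion.** The point holds as a contradiction about the primary endpoint that leaves the 0.05 unprotected, not as a demonstrated breach of it. The error rate is 0.05 if only the anxiety contrast is tested. It is about 0.08 to 0.10 if either of two unadjusted scales may count, and higher with more measures. These figures rest on two-sided tests, equal correlations between 0 and 0.8, and an either-scale claim that the text permits but does not announce. The analyses already reported do not change this conclusion. They only make it more useful to record what was seen and whether it was split by arm.

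**What to change.** In Primary Outcomes and Statistical Analysis:

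1. Name one primary test: the between-arm difference in GAD-7 change from week 0 to week 26, estimated from the planned random-effects model using all visits.
2. Make depression, SF-12, WSAS, contrasts at other visits and any cutoff-based result secondary.
3. Remove mood, cutoff scores, sensitivity and the open "etc" from the sentence on where the effect will be seen.
4. Fix this before any follow-up data are seen by arm, and state whether the depression and SF-12 analyses already reported were pooled over arms.
5. Restate the power for GAD-7 alone, with any baseline or between-visit correlation that it relies on.

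The wording change is about one paragraph in an amendment. There are two real costs. A benefit confined to depression could no longer be claimed as a primary result. The stated power would also have to rest on d = 0.13, where the simple comparison gives about 0.65 at 650 per arm, so the 0.90 would need to be justified by gains from baseline adjustment or repeated measures, or be revised.

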## Results

The study is ongoing and the first wave data collection is complete; we are analyzing data from the baseline and weeks 2-26. The study is ongoing at week 26, we have analyzed the preliminary baseline data and weeks 2 and 4 short and long follow-ups to understand the ongoing trajectory of depression. Until now, 453 individuals in the age group of 18-72 years have responded to the study invitation emails.

The trial is currently in the ethics approval process. Thus far, ethics approval has been granted by the REB of CAMH, and participant recruitment is ongoing. The study will be conducted in accordance with the REB-approved study documents and the determinations (including any limitations) of the REB, and in compliance with the REB’s requirements.

## Discussion

### Anticipated Findings

At baseline, with regard to gender and race, a greater proportion of participants are female (n=359, 75.57%) and White (n=335, 67.95%). We aim to generalize this study to the Canadian population; hence, we have been weighting samples at the census level based on gender and province to make this study representative. Weighing of the sample will help us understand how generalizable the sample and advertisements are and whether they are adequately representative. The SF-12, measuring mental and physical health, has revealed a significant decline in mental health from baseline to short and long follow-ups in this study. It is too early to discuss how this will develop longitudinally, but the preliminary results suggest a larger decline in mental health than in physical health in the Canadian population.

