**Objective:**

This study aims to better understand the effectiveness of the existing digital interventions in improving population mental health in Canada.

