**Results:**

The study was approved by the research ethics board of CAMH (Centre for Addiction and Mental Health, Toronto, Ontario, Canada). It is ongoing and participant recruitment is underway. As of August 2023, a total of 453 participants in the age group of 18-72 years have participated, of whom 70% (n=359) are female.

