### Participants and Recruitment

Adults (N=2000) will be recruited using both paid and free web-based advertisements (social networking sites, Google advertisements, Facebook, Instagram stories, Twitter, etc). The Facebook business account of CAMH will be used to advertise the study and recruit participants. In the case of web-based advertisements, participants will click on a link in the advertisement that will direct them to a REDCap (Research Electronic Data Capture) survey, which will screen them for eligibility (see Textbox 1 for inclusion and exclusion criteria). The project’s social media pages and CAMH’s page will be used for advertisements. Further, we will also approach the participants from other ongoing studies at CAMH including the Vaping Research Panel, Smoking Panel, and those who had agreed to be contacted for future studies. We will not cold contact previous participants; we will ensure that initial contact with the participants is made by the research staff who had previously contacted and are known to them. This will help establish trust and compliance for the Let’s Act on Mental Health study.

Inclusion and exclusion criteria for the study.

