### Inclusion Criteria

Inclusion criteria are (1) being aged 18 years or older, (2) residing in Canada and speaking either English or French, (3) able to complete study measures in English, (4) willing or interested to use the digital interventions to improve their mental health, and (5) having internet access. Furthermore, concomitant psychotropic medication use will be allowed.

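### Census weighting on gender and province cannot make this self-selected sample representative of Canada, so the population statements should be limited to the eligible population sampled

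*Protocol article*

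**What the plan says.** The Abstract gives the objective as "to better understand the effectiveness of the existing digital interventions in improving population mental health in Canada". Under Anticipated Findings the article states "We aim to generalize this study to the Canadian population" and, as the means to that end, "we have been weighting samples at the census level based on gender and province to make this study representative". The next sentence adds that weighting "will help us understand how generalizable the sample and advertisements are and whether they are adequately representative". The section closes its SF-12 discussion with "the preliminary results suggest a larger decline in mental health than in physical health in the Canadian population".

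The people who can be in the sample are described elsewhere:

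- The Inclusion Criteria require participants to be "able to complete study measures in English, (4) willing or interested to use the digital interventions to improve their mental health", and to have internet access.
- The Exclusion Criteria remove people at risk for suicide.
- Participants and Recruitment relies on web advertisements and adds that "we will also approach the participants from other ongoing studies at CAMH including the Vaping Research Panel, Smoking Panel", together with earlier participants who agreed to further contact.

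Trial Design, Primary Outcomes and Statistical Analysis name age, sex or gender, race and socioeconomic status as subgroups in which the effect may differ. Ethical Considerations lists age, race and ethnicity, and education among the baseline items. Statistical Analysis specifies a linear random effects model under intention to treat and mentions no weights.

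**The concern.** The only weighting variables named are gender and province. The features that most clearly separate this sample from the adult population are interest in digital help, language of completion, internet access, suicide risk at screening and membership of a research panel. None of these is in the weights.

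Two kinds of conclusion are exposed. The first is descriptive: a statement that mental health has declined among Canadians has no protection from randomisation and rests entirely on representativeness. The second is transport: an effect estimated in this sample and called the Canadian effect will be wrong if the effect varies with characteristics the weights ignore, which the third research question treats as possible. The article also wants its economic results to inform health care resource allocation in Canada, so the reach of the claim matters. The Limitations section does not mention selection.

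**Working it through.** **What the weights can do.** Let g be gender, p province, and S = 1 mean that a person was eligible and joined. With cell weights, the weighted mean of any quantity Y (an SF-12 change, or an individual treatment effect) is

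Σ P(g,p) · E[Y | g, p, S = 1],

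whereas the population value is Σ P(g,p) · E[Y | g, p]. The difference is

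Σ P(g,p) · {E[Y | g, p, S = 1] − E[Y | g, p]}.

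The weights fix P(g,p) and leave the bracket untouched. The bracket vanishes only if, within gender and province, those who joined are like those who did not. If the weights are built from margins rather than joint cells, the same limit applies.

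**Setting the sections side by side.**

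- *Interest and internet access* are entry conditions. People without them have no chance of inclusion, so no weight can represent them.
- *Language* works the same way. French speakers may enter, but only if they can complete measures in English, although the Introduction describes a portal offered in both languages. Within each province, those who can do so are weighted to stand for those who cannot.
- *Suicide risk* at screening is an exclusion, so the upper end of severity is cut off.
- *Recruitment source* (advertisements, vaping and smoking panels, former participants) is not a weighting variable.
- *Age, race and education* are collected and could be weighted on, but are not named as weighting variables.

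The size of the bracket cannot be computed, because the article gives no data on non-participants.

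**The reported female share.** The Abstract reports "a total of 453 participants in the age group of 18-72 years have participated, of whom 70% (n=359) are female". Anticipated Findings gives the same 359 as 75.57%.

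- 359/453 = 79.2%, which matches neither figure.
- Implied denominators: 359/0.70 = 513 and 359/0.7557 = 475.
- The White share in the same sentence of the Discussion (335 at 67.95%) implies 335/0.6795 = 493.

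**Conditional cost in precision.** This applies only if weights entered the arm comparison. With sample female share f and census female share P, the Kish design effect from gender alone is P²/f + (1 − P)²/(1 − f). The article does not give P, so 49% to 52% is assumed. Everyone not female is treated as one group.

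Example for f = 0.7557, P = 0.51: 0.2601/0.7557 + 0.2401/0.2443 = 0.344 + 0.983 = 1.33.

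| Sample female share | P = 49% | P = 51% | P = 52% | 2000 divided by design effect |
|---|---|---|---|---|
| 70% (Abstract) | 1.21 | 1.17 | 1.15 | 1653 to 1733 |
| 75.57% (Discussion) | 1.38 | 1.33 | 1.30 | 1447 to 1537 |
| 79.2% (359/453) | 1.56 | 1.49 | 1.45 | 1285 to 1378 |

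Standard errors would grow by the square root of the design effect: √1.154 = 1.07 to √1.556 = 1.25, that is, by 7% to 25%. Province weights would change this by an amount that cannot be computed, because neither the sample nor the census distribution by province is given.

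**The case against.** The strongest reply is that the main question is a randomised contrast between the portal and usual care. Selection at entry does not bias that contrast for the people enrolled. The portal is voluntary and web-based, so interest and internet access partly define its users. The panels supplement open advertising, and their share of the sample is not reported. The article also presents weighting partly as a way to find out whether the sample is representative. All of this stands. It does not rescue the wording, because the same section states representativeness as the purpose of the weights and then speaks of the Canadian population without qualification.

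A reader might infer that the weights cost the trial precision. The documents do not support that as a flat statement: weighting appears only in the Discussion, beside baseline shares and early SF-12 trends, and the analysis section includes no weights.

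A reader might also infer from the White share that the sample is racially unbalanced. No census benchmark is given, so this cannot be judged. The planned subgroup interactions do not need race or age in the weights.

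Finally, it can fairly be said that adding more variables to the weights will not cure selection on interest or language. That is correct, and it is why the change of wording matters more than the extra variables.

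**Conclusion.** The point holds for the claim of representativeness. Gender and province weighting does not give the study the property the article ascribes to it. The statement about decline in the Canadian population, and any extension of the effect to all Canadians, are unsupported. The direction and size of the error are unknown.

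It would go too far to conclude that the trial cannot answer its effectiveness question: this point does not undermine the internal validity of the comparison for people like those enrolled.

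The precision loss is conditional on weights being used in the arm comparison. The design effect of about 1.15 to 1.56 then rests on the assumed census share, on three inconsistent sample shares, and on the early recruits' gender mix holding for all 2000.

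The mismatch in the female share is a separate reporting inconsistency. It does not show that the weights themselves are wrong, since they would presumably be built from the data rather than from a printed percentage.

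**What to change.** 1. Replace the claims of representativeness and of findings for the Canadian population with the population sampled: adults in Canada with internet access, able to complete measures in English, interested in digital interventions, and not at suicide risk at screening. Add this selection to the Limitations.
2. State whether weights enter the effect analysis, and confirm that the unweighted intention-to-treat contrast is primary.
3. Make any population-weighted estimate secondary. Add census margins for age, race/ethnicity and education to gender and province, and say that this still does not correct selection on interest or language.
4. Reconcile the count of 359 with its denominator and give one female share throughout.

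The cost is wording plus one further weighting step on variables already collected. The downside is a wider interval for the secondary weighted estimate and a narrower claim about whom the results describe.
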